## Abstract

**Abstract:**

**Trial Registration:**

Australian and New Zealand Clinical Trials Registry Number 12610001064099

## Background

Emergency Department (ED) overcrowding is an international phenomenon[1]. Overcrowding is associated with mortality[2], delay to time critical therapy[3,4], patient dissatisfaction[5] and ambulance ramping, where paramedics are unable to deliver patients to ED due to a lack of available beds.

In Australia, there are over 7 million hospital ED episodes of care per year with up to 25% of patients arriving in ED by ambulance[6]. Estimates of the proportion of these ED cases that are primary care patients vary according to the definition and scope of primary care[7], but a reasonable proportion of cases that present to ED by ambulance may be equally suited to care in the community by a primary care service.

There are many reasons why people call an ambulance in addition to a medical emergency. There may be inability to access alternative health care; issues associated with chronic illness and disability; requirements for advice and reassurance; and psychosocial reasons. Many patients access health care through the ambulance service without necessarily believing they need transport to hospital, yet paramedics in some jurisdictions are governed by the duty of care that requires them to render assistance and care for the patient until they handover to another health service. In practice this means that the patient may be transferred to ED even if the patient does not require emergency care.

There is evidence from cluster and before-after studies that paramedics with extended skills can mange low-risk patients in the community without hospital transfer[8,9]. However other studies using paramedics as an assessment and referral service to divert cases away from ED have yielded conflicting results[10]. This trial has been designed to provide an alternative care path for patients that call an ambulance for minor injury and illness. The aim of the trial is to determine whether paramedic referral to a rapid response primary care service in the patient's own residence is clinically effective, safe and an efficient use of resources.

## Methods/Design

### Ethical considerations

The study has received human research ethical approval from Edith Cowan University (5249 SIM), the Department of Health Western Australia (#2010/45) and the Silver Chain Association of Western Australia (EC App 066).

### Study setting

The study will commence in 2011 and be conducted in metropolitan Perth, Western Australia - a city with a population of over one million people serviced mainly by a single not-for-profit ambulance service (St John Ambulance Australia WA Inc) contracted by the government. The ambulance service transport adult patients to one of three tertiary or four district ED within the metropolitan area. Currently there are in excess of 100000 ambulance transfers to these ED annually.

### Study design

A randomised controlled trial, with consenting eligible patients randomised to either the intervention or usual care (ED transfer).

### Eligibility criteria

#### a. Inclusion

To be eligible for the trial patients will have been attended by paramedics in their own residence for *any *of the following suspected clinical conditions

1. Isolated minor injury from low risk mechanism e.g. simple laceration, isolated distal limb injury, simple contusion

2. Simple infection e.g. below knee cellulitis, influenza-like illness

3. Hardware problem e.g. blocked or displaced bladder catheter

#### b. Exclusion

Patients will be excluded if they meet *any *of the following criteria

1. Age < 16 years

2. Third trimester pregnancy

3. Not in own residence when attended by paramedics

4. Residence is unsafe environment for patient (e.g. living alone and requiring supervision) or staff

5. Glasgow Coma Score < 15

6. SaO_2 _< 95% in room air

7. Heart rate > 100/min

8. Systolic BP < 100 mm Hg

9. Severe pain requiring narcotic analgesia

10. Paramedics assess patient as being unsuitable to wait up to four hours for assessment and management

### Consent and enrolment procedures

Patients will be enrolled by paramedics that have been trained in the research protocol. Eligible patients will be identified by the paramedics using a checklist, and patients will be provided with verbal and written information in an Information and Consent Form. Written consent will incorporate agreement to being randomised to the intervention or control arm, to allow access to medical records and to allow a follow up telephone call at 28 days post enrolment. If patients do not consent to the study they will be transported to hospital as per usual practice. Patients may choose to withdraw consent at any time without prejudice. Patients randomised to the intervention arm will be advised to make a second call for paramedic assistance if they feel their condition has worsened prior to the arrival of the home hospital team.

Upon attainment of written consent, paramedics will call the central ambulance emergency call centre to confirm suitability for the trial with a Clinical Support Officer, provide information about the enrolment and obtain trial allocation. Patients will be randomised through a computer generated randomisation process at the call centre, and the paramedics, at the scene, informed to either refer the patient by telephone to the priority response home hospital service (intervention arm) or transport the patient to ED (control arm).

### Intervention

The intervention arm will be a priority response home hospital service run by the Silver Chain Association of Western Australia that will visit the patient in their own residence within four hours of paramedic referral. A nurse practitioner or clinical nurse specialist will provide the initial episode of care with 24 hour medical cover provided by an on-call roster of general practioners and specialists. Assessment, investigation and treatment as required will occur in the community. After the initial episode of care in their residence the patient may be discharged from the care of the service; have ongoing therapy at home over ensuing days e.g. IV antibiotics; or if needed referred to an ED.

### Control

The control is transfer of the patient to a public hospital ED for medical assessment, investigation and treatment as required.

### Outcome measures

#### a. Primary

The primary outcome measure is the proportion of patients requiring one or more episodes of unplanned medical attention (in or out of hospital) in the first 48 hours.

#### b. Secondary

1. Proportion of patients requiring 2nd ambulance attendance prior to the arrival of the primary care team.

2. Number of ambulance transports of patients to ED following referral to the intervention.

3. Proportion of patients referred to ED in the control arm that did not wait for assessment/treatment

4. Time to first contact with definitive care provider (ED and home hospital team).

5. Number of investigations performed

6. Number of calls to ambulance call centre within 48 hours.

7. Number of episodes of contact with healthcare providers in next 7 days.

8. Number of episodes of ED attendance within the next 7 days.

9. Hospital admissions within the next 7 days.

10. Adverse events within the next 7 days.

11. Deaths within the next 7 days.

#### c. Cost benefit

A cost benefit analysis will be performed to reveal economic outcomes. Difference between the annualised extra fixed and variable costs and the annualised savings in health system costs will determine the net benefit, if any, of the intervention.

Costs will be calculated as fixed costs (e.g. equipment costs depreciated over the life of the equipment giving annual costs) and variable costs (e.g. labour costs for the Home Hospital program service and paramedic training costs). Benefits will be calculated through differences between the intervention and control groups in ambulance usage, hospital separations and ED visits.

#### d. Patient satisfaction

Patient satisfaction with whichever arm they were randomised to will be measured at 28 day telephone follow up using a series of rating scale questions. Participants will be asked to report on satisfaction with the timeliness of the services, the explanation received, the care received, convenience of the service, follow up arrangements, staff attitudes and overall service. They will also be asked about their perception of safety within the service, perception of adequate diagnosis and symptom relief, and their preference for treatment at hospital or home hospital.

### Data collection mechanisms

Initial enrolment data will be collected using preformatted data sheets to be completed by paramedic staff. Once randomised, patients will be followed up by research staff employed specifically for the project. Staff will use electronic hospital databases, supplemented by individual patient medical records where necessary, to determine resource utilisation and outcome data for patients randomised to the comparator arm. Staff will use existing databases to collect similar data on patients in the intervention arm. 28 day follow up will be by telephone call supplemented by data from the data linkage unit at the Health Department of Western Australia.

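### Outcome sources are named separately by arm, and no source that would be expected to record out-of-hospital care is tied to the 48-hour primary endpoint in both arms

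*Protocol article*

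**What the plan says.** The primary outcome (Protocol article, Outcome measures, a. Primary) is the proportion of patients with "one or more episodes of unplanned medical attention (in or out of hospital) in the first 48 hours".

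Data collection mechanisms then gives the sources arm by arm:

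- Comparator: "Staff will use electronic hospital databases, supplemented by individual patient medical records where necessary, to determine resource utilisation and outcome data", with the sentence limited to patients randomised to that arm.
- Intervention: "Staff will use existing databases to collect similar data on patients in the intervention arm". These databases are not named.
- Not limited to one arm: "28 day follow up will be by telephone call supplemented by data from the data linkage unit" at the state health department.

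The content of the call is described only under d. Patient satisfaction, where satisfaction "will be measured at 28 day telephone follow up using a series of rating scale questions". The listed items are satisfaction, perceptions of safety, diagnosis and symptom relief, and preference for place of treatment. Healthcare contacts in the first 48 hours are not among them. Consent and enrolment procedures obtains agreement to record access and to the call from all patients before allocation.

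**The concern.** The endpoint reaches outside hospital, but the source named for the comparator arm is a hospital one. A patient discharged from ED who sees a general practitioner the next day meets the endpoint, yet would not be expected to appear in a hospital database. Whether the medical-record supplement would show such a visit is not stated. For the intervention arm, the reader cannot tell whether the same systems are searched.

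If the two arms are captured with different completeness, the observed risk ratio differs from the true one, and the non-inferiority conclusion can change with it. This is bias, not noise. A larger sample does not remove it, and neither the chi-square test nor the relative risk in the Statistical plan corrects it. The Discussion names inferior clinical outcomes in the intervention arm as the trial's one major risk, and this endpoint is the main means of judging that. The same issue affects the count of healthcare contacts over 7 days among the secondary outcomes.

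**Working it through.** **Inputs from the protocol article (Sample size estimates).** Event rate 5%; non-inferiority margin risk ratio 1.5, which at 5% is 7.5% or 2.5 percentage points; α = 0.05; β = 0.2; 940 per group. Sidedness is not stated.

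**Reproducing 940.** On the difference scale with one-sided α = 0.05:

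n = (1.645 + 0.842)² × 2 × 0.05 × 0.95 / 0.025² ≈ 940 per group.

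This matches. One-sided 0.025 would give 1194, and the log risk ratio scale at one-sided 0.05 would give 1430. I therefore use one-sided 0.05 and show both scales, because the margin is worded as a ratio while the sample size matches the difference.

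**Bias.** Let the capture in an arm be the share of true events that its sources find. Then:

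observed rate = true rate × capture

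observed RR = true RR × (intervention capture / control capture)

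**Probability of declaring non-inferiority** (normal approximation, n = 940 per arm, observed rates pC and pT):

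- Ratio scale: Φ{[ln 1.5 − ln(pT/pC)] / √[(1−pC)/(n·pC) + (1−pT)/(n·pT)] − 1.645}
- Difference scale: Φ{[0.025 − (pT − pC)] / √[pC(1−pC)/n + pT(1−pT)/n] − 1.645}

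The documents give no capture rates. Those below are assumptions, shown as a range.

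**Control arm under-captured, intervention complete, true RR 1.0**

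| Control capture | Observed RR | Power, ratio | Power, difference |
|---|---|---|---|
| 100% | 1.00 | 0.645 | 0.800 |
| 90% | 1.11 | 0.423 | 0.653 |
| 80% | 1.25 | 0.214 | 0.470 |
| 70% | 1.43 | 0.077 | 0.285 |

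Worked line for 80%: pC = 0.05 × 0.8 = 0.04 and pT = 0.05.

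- Ratio: the standard error is √(0.96/37.6 + 0.95/47) = 0.214. Then (0.405 − 0.223)/0.214 − 1.645 = −0.79, and Φ = 0.21.
- Difference: the standard error is √[(0.0384 + 0.0475)/940] = 0.00956. Then (0.025 − 0.010)/0.00956 − 1.645 = −0.08, and Φ = 0.47.

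In events, 940 × 0.05 = 47 are expected per arm, so 80% capture means about 9 control events missed.

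**Intervention arm under-captured, control complete, true RR 1.5**

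| Intervention capture | Observed RR | False non-inferiority, ratio | False non-inferiority, difference |
|---|---|---|---|
| 100% | 1.50 | 0.050 | 0.050 |
| 90% | 1.35 | 0.140 | 0.170 |
| 80% | 1.20 | 0.315 | 0.414 |
| 70% | 1.05 | 0.560 | 0.715 |

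**Both arms under-captured.** Suppose 20% of events are out of hospital, the control sources find none of them and the intervention sources find half. Capture is then 80% and 90%. A true RR of 1.0 is observed as 1.125, with power 0.369 (ratio) or 0.693 (difference). If both arms miss the same share, the expected risk ratio is unchanged.

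**The case against.** The strongest reply is that this is a condensed article. Full source lists and call scripts commonly sit in the full protocol, and their absence here is no finding. Several passages also suggest that the gap is narrower than the two source sentences imply:

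- The call and the data linkage cover both arms. Linkage data cannot supplement satisfaction ratings, so the 28-day follow-up may well collect healthcare use too. The satisfaction section does not say that the call contains nothing else.
- The secondary outcomes require ED attendances and admissions to 7 days, without restriction by arm. The Cost benefit section compares the two groups on ambulance use, hospital separations and ED visits. Hospital data on intervention patients are therefore planned.
- The unnamed databases may include the same hospital systems. Different records for the index episode are unavoidable when one arm is treated in ED and the other at home.

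Most of this stands, and it rules out stronger readings. A reader might infer that hospital events go unsearched in the intervention arm, which the outcomes just listed contradict. A reader might infer that the home service logs all out-of-hospital contacts as they happen, but nothing says so, and its own visits may be planned ongoing therapy. A reader might take half of the endpoint to be invisible, but no in/out-of-hospital split is given.

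One thing is not answered. The article does not merely leave the sources out: it assigns them by arm, and the one it names for the comparator does not fit an endpoint that includes "unplanned medical attention (in or out of hospital) in the first 48 hours". No section links the call or the linkage to that endpoint, or says that the linkage covers care outside hospital.

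**Conclusion.** The concern holds as a should-fix point. Followed as written, the comparator source would be expected to miss out-of-hospital events, and nothing states that the primary endpoint is ascertained in the same way in both arms.

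The best-documented direction is a control rate that is too low, which makes it harder to show non-inferiority. With capture of 80% in control and 100% in intervention, truly equal arms would appear as a risk ratio of 1.25, and power would fall to 21% (ratio) or 47% (difference). Those sizes rest on assumed capture rates, on one-sided 0.05, and on the 5% event rate. They would shrink if the intervention sources also miss such contacts, or if the call and linkage already supply them.

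A reader might infer that the plan favours a false claim of non-inferiority. The documents do not support that. It would need poorer capture in the intervention arm than in control, which the wording leaves open but does not state. The second table shows what would follow in that case; it is not a prediction. The sample size of 940 is not affected by this point.

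**What to change.** Amend Data collection mechanisms so that the 48-hour and 7-day outcomes are determined for every randomised patient, whatever the arm, from one list of sources: hospital and ED databases with record review, the ambulance call-centre log, the home-hospital service records and the data linkage. Add one scripted question on out-of-hospital care in the first 48 hours to the planned 28-day call, worded identically in both arms, and state that the answer contributes to the primary endpoint.

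The cost is some extra look-up time for research staff already employed and a few more questions in a call to which patients already consent. No new visits are needed. Recall of a 48-hour window four weeks later remains a limitation, though one common to both arms. The change is best made before enrolment, since contacts not asked about may not be recoverable afterwards.

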### Sample size estimates

Based on an estimate of 5% of patients having an unplanned episode of care within 48 hours, to detect non-inferiority defined as a risk ratio no greater than 1.5 between the intervention and control groups a sample size of 940 patients in each group will be required (if α = 0.05 and β= 0.2). We estimate 10% of the 100000 annual ambulance transfers will be eligible for the trial so anticipate being able to recruit the requisite sample size in less than one year.

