### Statistical plan

We will use summary descriptive statistics for the study population. Dichotomous outcomes will be compared between the intervention and comparator groups using Pearson's chi square test and by calculating relative risk. Continuous outcomes will be compared using an independent t test for normally distributed data and Mann Whitney U test for non-parametric data. Cost benefit will be expressed in dollar terms. Patient satisfaction outcomes will be largely descriptive.

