## Discussion

This trial is a methodologically rigorous and adequately powered evaluation of an alternative to hospital transfer for low acuity patients calling an ambulance service. There are large potential healthcare benefits in terms of reducing ED overcrowding, increasing paramedic availability, reducing ambulance ramping, cost savings and improving patient satisfaction. The study outcomes will provide important information on the safety and quality of assessment and care in the home for conditions which would otherwise result in a presentation to ED.

This is the first time that paramedics will be involved in a trial in which their assessment determines suitability for handover to a service outside of an ED. The clinical processes and pathways established in the trial will therefore provide evaluated practice as a basis for future health policy.

The trial has one major risk - inferior clinical outcomes associated with either misdiagnosis or inadequate therapy in the intervention arm. Although both paramedic and nurse practitioners are highly experienced health professionals and will have immediate access to specialist and generalist medical practitioners, there will be no medical diagnostician in the direct care of the vast majority of intervention arm patients. However we anticipate with careful patient inclusion and exclusion criteria and well trained staff, that we can select a sufficiently low risk study population and show clinical non-inferiority between the groups. We anticipate benefits to lie in cost savings and patient satisfaction.

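### 940 per group fits an absolute margin of 2.5 percentage points; for the stated risk ratio margin of 1.5 the power is about 64%, not 80%

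*Protocol article*

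**What the plan says.** The section on sample size estimates starts from "Based on an estimate of 5% of patients having an unplanned episode of care within 48 hours" and concludes that "to detect non-inferiority defined as a risk ratio no greater than 1.5 between the intervention and control groups a sample size of 940 patients" per group is needed ("if α = 0.05 and β= 0.2"). It gives no absolute margin and does not say whether α is one-sided or two-sided.

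The endpoint is binary: the "proportion of patients requiring one or more episodes of unplanned medical attention (in or out of hospital) in the first 48 hours". The statistical plan compares dichotomous outcomes "using Pearson's chi square test and by calculating relative risk". No risk-difference analysis is planned, so the margin and the planned effect measure are both ratios.

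The discussion then says: "This trial is a methodologically rigorous and adequately powered evaluation".

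**The concern.** At a control rate of exactly 5%, a risk ratio of 1.5 and a difference of 2.5 points describe the same pair of rates, 5% and 7.5%. It is easy to treat them as interchangeable when sizing a trial, but as tests they differ. A fixed absolute margin is a known number. A ratio margin is 1.5 times a control rate that the trial must itself estimate, so the uncertainty in that rate enters the comparison with more weight. The ratio test needs more patients.

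If 940 came from the absolute calculation, the trial lacks the stated power for the stated hypothesis. The discussion names inferior clinical outcomes in the home arm as the trial's one major risk, so this is its central inference. An equivalent service could too easily end with an inconclusive result. If the scale is left open, the choice between ratio and difference could also decide the conclusion after the data are known.

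**Working it through.** **Inputs.** From the sample size section: 5% event rate, risk ratio margin 1.5, α = 0.05, β = 0.2, 940 per group. Assumed: the true rate is 5% in both arms, allocation is 1:1, and there is no loss to follow-up. Normal quantiles: 1.645 (one-sided 5%), 1.960 (one-sided 2.5%), 0.842 (80% power).

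**Step 1: reproduce 940.** Risk difference, margin 0.075 − 0.05 = 0.025, one-sided 5%:

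n = (1.645 + 0.842)² × 2 × 0.05 × 0.95 / 0.025² = 6.183 × 0.095 / 0.000625 = 939.7, so 940.

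This is an exact match. The same formula at one-sided 2.5% gives 1,194, so 940 also requires α to be one-sided 5%. A superiority comparison of 5% with 7.5% gives 1,159 (one-sided) or 1,471 (two-sided). No other variant tried came close to 940.

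**Step 2: the sample size for the stated margin.** On the log risk ratio scale the variance is 2 × (0.95/0.05)/n = 38/n, and ln(1.5) = 0.4055:

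- one-sided 5%: n = 6.183 × 38 / 0.4055² = 1,429.04, so 1,430 per group
- one-sided 2.5%: n = 7.849 × 38 / 0.4055² = 1,814.2, so 1,815 per group

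The Farrington-Manning score test for a ratio gives 1,449 and 1,834. The linearised form tests p_T − 1.5 p_C, with variance 0.0475 × (1 + 1.5²) = 0.0475 × 3.25. It gives 1,528 and 1,939. The linearised form shows the cause: the difference formula includes the control-arm variance, but not the factor of 1.5 on the control rate, which multiplies that variance by 2.25.

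**Step 3: power at 940 per group.** SE(log RR) = √(38/940) = 0.201.

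- one-sided 5%: Φ(0.4055/0.201 − 1.645) = 0.645
- one-sided 2.5%: Φ(0.4055/0.201 − 1.960) = 0.523

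| Test at 940 per group | One-sided 5% | One-sided 2.5% |
|---|---|---|
| Ratio 1.5, log-RR formula | 64.5% | 52.3% |
| Ratio 1.5, log-RR Wald, exact enumeration | 64.2% | 52.1% |
| Ratio 1.5, Farrington-Manning, exact enumeration | 64.4% | 52.6% |
| Ratio 1.5, linearised formula | 62.0% | 49.6% |
| Difference 2.5 points, exact enumeration | 80.0% | 70.2% |

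On the ratio scale, 940 per group has 80% power at one-sided 5% only for a margin of exp((1.645 + 0.842) × 0.201) = 1.65.

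**Step 4: can the scale change the conclusion?** Take 47 control events (5% of 940) and one-sided 95% upper limits. With 50 intervention events the Wald ratio limit is 1.473, which passes. With 51 it is 1.50005, which just fails, although the score test passes. With 54 the difference limit is 2.46 points, which passes, while the ratio limit is 1.58, which fails. With 55 both fail. Under true equivalence at 5%, about 16% of trials would pass on the difference and fail on the Wald ratio; the reverse occurs in about 0.02%.

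**The case against.** - **The formula is not named.** The 2.5-point origin is therefore an inference. That is so, but the match is exact, and the shortfall does not depend on it: wherever 940 came from, it does not give 80% power for a ratio of 1.5 at 5%.
- **The 95% confidence interval is not the protocol's.** The text says only α = 0.05. This stands: 64% is the main figure, because it grants the favourable one-sided reading, and 52% applies only if a two-sided 95% interval is used.
- **Power depends on the true rate, and 5% is an estimate.** On the log-RR formula at one-sided 5%, power is about 72% at 6% in both arms, 78% at 7% and 80% at 7.5%. It is also about 80% if the true rates are 5% (control) and 4.5% (intervention). But it falls to 46% at 3%. The stated power must hold for the stated inputs, and it does not.
- **The band of disagreement is narrow.** With 47 control events it is 51 to 54 intervention events, and 51 is borderline. The counts are few, but they lie close to equality, which is why about one equivalent trial in six falls in such a band.
- **Low power does not produce false claims of non-inferiority.** This is correct if the ratio margin is kept in the analysis. The harm is then an inconclusive trial and an unsupported claim of adequate power.

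**Conclusion.** The concern holds. The margin, event rate, α, β and sample size printed in one section do not agree, and an analysis plan written later cannot make them agree. For the stated risk ratio margin of 1.5, 940 per group gives about 64% power at one-sided 5% (62% to 64.5% across methods), not 80%. The chance of missing non-inferiority for an equivalent service is about 36% instead of 20%. With a two-sided 95% interval, power is about 52% and the chance of missing is about 48%. These figures assume a true rate of 5% in both arms and no losses. The discussion's claim about power is not supported for the hypothesis as stated. This should be corrected before data are seen.

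**What to change.** Put the margin, test, α and power on one scale, and state that α is one-sided. There are two ways that need no extra patients:

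- **(a) Absolute margin.** State the margin as 2.5 percentage points (5% to 7.5%) at one-sided α = 0.05, test the primary outcome on the risk difference, and report the relative risk as supporting. 940 per group then gives 80% power at a 5% rate. This redefines the margin and needs its own justification: at a control rate of 3% it would allow a ratio of 5.5/3 = 1.83.
- **(b) Ratio margin.** Keep 1.5 and restate the power of 940 per group as about 64% (one-sided 5%) or 52% (95% confidence interval). Remove the claim of adequate power from the discussion.

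The cost is wording in the sample size section and the analysis plan; under (b) the stated power is also less favourable. If the sponsor wants both the ratio of 1.5 and 80% power, the sample must grow to about 1,430 to 1,450 per group at one-sided 5%. That is at least 490 more per group, or 980 in total, and is not a cheap change.
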